### Blinding

Physicians (primary investigators and investigators) enroll the patients. An investigator (coordinator) fully knowledgeable of all protocols, policies, procedures, and definitions in the study allocates the treatment. Patients, care providers, and evaluators are blind to treatment allocation. Unblinding is permissible only in the case of significant improvement or significant deterioration of primary outcome measures. Interim analyses will be performed by the study coordinator and the principal investigator not involved in the direct evaluation of patients.

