### Enrollment and Randomization

After potential participants have signed the informed consent, their eligibility is evaluated based on the inclusion/exclusion criteria (Figure 1). If eligible, their demographic characteristics, medical history, and physical examination are assessed; both eyes are evaluated for visual acuity [Early Treatment Diabetic Retinopathy Study (ETDRS) chart test], retinal thickness (non-invasive optical coherence tomography, OCT), and retinal microvascular abnormalities (fundus biomicroscopy and/or fluoroangiography). Laboratory tests are also carried out to determine circulating levels of PRL, glycated hemoglobin, alanine aminotransferase, thyroid-stimulating hormone, and creatinine (Figure 1). The evaluations confirm eligibility, allow for the distribution of patients, and set the baseline reference for treatment comparisons. DME is diagnosed by means of ophthalmoscopy and OCT measurements of central retinal thickness (30). Patients are classified as having NPDR and PDR according to the international clinical DR severity scale (31). DME and NPDR patients are randomized in a 1:1 ratio to receive levosulpiride (25-mg orally TID for 4 weeks) or placebo (lactose pill orally TID for 4 weeks). PDR patients requiring vitrectomy (due to non-clearing vitreous hemorrhage, tractional retinal detachment, and/or severe neovascular proliferation) are randomly split 1:1 to receive levosulpiride (25-mg orally TID) or placebo (lactose pill orally TID) 1 week before undergoing vitrectomy. Patients requiring antiangiogenic therapy for the treatment of clinically significant DME are randomized to receive levosulpiride (25-mg orally TID) or placebo (lactose pill orally TID) during the 12 weeks of standard ranibizumab intravitreal therapy (0.5 mg every 4 weeks) (Figure 1). In all groups, the study medication is taken on top of standard therapy for diabetes, blood pressure control, or other medical conditions. Specifically, this therapy includes metformin, sulfonylureas, dipeptidyl peptidase-4 inhibitors, acarbose, insulin, ACE inhibitors or angiotensin II receptor blockers, beta blockers, calcium antagonists, and/or diuretics, etc. In the case of adverse and intolerable effects of the study medication, the treatment is stopped and reported as a failure (32).

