### Outcome Measures

After enrollment, four study visits take place every 2 weeks during a follow-up period of 8 weeks in groups 1 and 2 (DME: placebo and levosulpiride) and groups 3 and 4 (NPDR: placebo and levosulpiride). For groups 7 and 8 (DME plus ranibizumab: placebo and levosulpiride) enrollment is followed by three visits, one every 4 weeks (at the time of ranibizumab intravitreal delivery). At each visit, the medical history, physical examination, adverse events, and primary and secondary outcomes are documented. For groups 5 and 6 (PDR requiring vitrectomy: placebo and levosulpiride), there is only one visit 1 week after enrollment, i.e., at the time of vitrectomy.

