#### Objectives

The objectives of the study are to evaluate the effect of prolonged exposure to PRL induced by levosulpiride on DME and DR progression, evaluate the effect of levosulpiride as a combination therapy with ranibizumab on DME progression, and whether the actions of levosulpiride occur *via* the intraocular incorporation of PRL and its conversion to vasoinhibins. Therefore, the primary endpoints of the study medication are changes from baseline of ophthalmologic parameters and of PRL and vasoinhibin levels in the vitreous.

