#### Secondary Outcome Measures

The secondary endpoints evaluate the safety of the study medication by measuring:
Blood pressureBlood glycated hemoglobinSerum glucoseSerum creatinineHyperprolactinemia-related side effects documented at each participant visit (32)Dopamine D2 receptor blocker side effects documented at each participant visit (32)

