### Data Collection and Analysis

The same physicians (ophthalmologists and endocrinologists) and laboratory technicians will collect and evaluate the data from all patients. Data are recorded in questionnaires, images and electronic quantitations (OCT, fundus biomicroscopy and fluoroangiography), and laboratory biochemical determinations. All images collected during the study are sent for re-assessment to a central evaluation center at the recruiting Institution to insure accurate evaluation. The coordinator of the study will continually examine the registry to insure all collected data are complete, accurate, and valid. Data logically inconsistent will be confronted with information in external database. Data collected on formatted paper forms are entered into a computer and electronic registries carefully reviewed by a third party to identify missing data, invalid or erroneous entries, and inconsistent data. Any data review activity and remediation efforts will be documented. Statistical methods evaluate continuous and categorical variables, the association between hormonal levels and outcome, and the relative contribution of confounding factors. The study data will be stored in the recruiting Institute through private accessing codes and kept for up to 10 years following the publication of the study. The data information will then be destroyed.

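### The only permitted ground for unblinding is a change in the primary outcomes: the trigger is undefined, depends on the endpoint, and leaves out non-ocular safety

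*Protocol article*

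**What the plan says.** The Blinding section describes a double-blind trial: "Patients, care providers, and evaluators are blind to treatment allocation". It then gives one exclusive condition for lifting the blind: "Unblinding is permissible only in the case of significant improvement or significant deterioration of primary outcome measures". The next sentence turns to interim analyses, which are assigned to staff who do not themselves examine patients.

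The primary outcomes that act as the trigger are set under Objectives: "the primary endpoints of the study medication are changes from baseline of ophthalmologic parameters and of PRL and vasoinhibin levels in the vitreous". The ophthalmologic part is spelled out under Primary Outcome Measures as visual acuity, OCT, fundus and angiography findings. Tolerability sits elsewhere. Secondary Outcome Measures opens with "The secondary endpoints evaluate the safety of the study medication by measuring" and lists, among other items, side effects of raised prolactin and of D2 blockade.

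On adverse effects, Enrollment and Randomization says: "In the case of adverse and intolerable effects of the study medication, the treatment is stopped and reported as a failure". It does not mention the code.

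On timing, Outcome Measures says: "At each visit, the medical history, physical examination, adverse events, and primary and secondary outcomes are documented". Groups 1–4 have four follow-up visits two weeks apart, groups 7 and 8 have three visits four weeks apart, and groups 5 and 6 have a single visit at vitrectomy. On who assesses, Data Collection and Analysis says: "The same physicians (ophthalmologists and endocrinologists) and laboratory technicians will collect and evaluate the data from all patients".

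**The concern.** A code break normally rests on a need that is separate from the endpoint, typically that someone must know the allocation to look after a patient. Here the endpoint itself is the ground. Three problems follow.

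- **Selection by outcome.** If single patients can be unblinded on a large change, those whose blind is lifted are chosen by the quantity the trial is measuring. Their remaining visits still feed the primary analysis. Letter reading depends on the patient's effort and qualitative image reading on the grader's judgement, so both are open to influence if the arm becomes known.
- **Undefined terms.** No size of change, statistical test, or level (patient or group) is given, so two investigators could apply the sentence differently.
- **Safety left out.** Side effects are not primary outcomes. Read literally, a serious non-ocular event can never satisfy the condition, even where knowing the allocation would matter.

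**Working it through.** **Step 1. Read the rule against the outcome lists.** The permitted grounds are changes in primary outcomes and nothing else. Ocular worsening is a primary outcome and so is covered. Drug side effects are listed as secondary and so are not. The article elsewhere foresees effects bad enough to stop treatment, so the excluded situation is one the plan expects could arise.

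**Step 2. Where can later visits be affected?** A trigger at the first follow-up visit leaves 4 − 1 = 3 later visits in groups 1–4 and 3 − 1 = 2 in groups 7 and 8. In groups 5 and 6 it leaves 1 − 1 = 0, so this concern does not reach them.

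**Step 3. Illustrate how often a patient would meet the trigger.** The article gives no unblinding rate or threshold, so there is no figure to reproduce. Inputs:

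- Effect of 10 letters and SD of 10, both from Sample Size.
- SD of 10 read as the SD of change. This is an assumption, because the article does not say which SD it means. If 10 is the spread of a single-visit score with correlation ρ between visits, the SD of change is 10 × √(2(1 − ρ)), which equals 10 only at ρ = 0.5.
- Threshold t of 5, 10 or 15 letters in either direction (assumed).
- Mean change in each arm as shown (assumed), with normally distributed change.

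For mean change m, the share meeting the trigger at one visit on acuity alone is

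P(|X| ≥ t) = [1 − Φ((t − m)/10)] + Φ((−t − m)/10).

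At t = 10:

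- m = 0: [1 − Φ(1)] + Φ(−1) = 0.159 + 0.159 = 0.317 (before rounding the parts)
- m = +10: [1 − Φ(0)] + Φ(−2) = 0.500 + 0.023 = 0.523
- m = +5: [1 − Φ(0.5)] + Φ(−1.5) = 0.309 + 0.067 = 0.375 (before rounding the parts)

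The formula is symmetric in m, so −10 gives the same share as +10, and −5 the same as +5.

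| Mean change, placebo / drug | t = 5: placebo / drug | t = 10: placebo / drug | t = 15: placebo / drug |
|---|---|---|---|
| 0 / +10 (drug improves, placebo stable) | 61.7% / 75.8% | 31.7% / 52.3% | 13.4% / 31.5% |
| +5 / +15 (both improve) | 65.9% / 86.4% | 37.5% / 69.8% | 18.1% / 50.1% |
| −5 / +5 (equal and opposite) | 65.9% / 65.9% | 37.5% / 37.5% | 18.1% / 18.1% |
| −10 / 0 (drug prevents decline) | 75.8% / 61.7% | 52.3% / 31.7% | 31.5% / 13.4% |

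Every row has the same 10-letter difference between arms. The gap in eligibility for unblinding is positive, zero or negative depending on where that difference comes from.

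**The case against.** **The sentence may concern the group, not the patient.** It never speaks of an individual code, and a sentence on interim analyses follows directly. Lifting the blind when accumulating data show clear benefit or harm would also explain why improvement is listed. This stands as a possible reading. On it, the shares above do not apply and improvement can be a sensible trigger. The rule would still depend on observed results, leave the criterion undefined, and exclude non-ocular safety.

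**A reader might infer that unblinding will be commoner in an effective arm.** The text does not support that. Deterioration is also a trigger, and the table shows the gap vanishing or reversing. The Objectives speak of effects on disease progression, so a drug that mainly prevents decline is a plausible scenario.

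**A reader might take the percentages as unblinding rates.** They are not. The rule permits unblinding and does not require it, and both the threshold and the SD of change are assumed.

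**A reader might infer that evaluators will be told the arm.** The article does not say so. A coordinator allocates treatment, and the interim analysts do not examine patients. Equally, nothing says the evaluators are shielded after a code break, and the same physicians assess everyone. Some patients who worsen also leave follow-up under the Elimination Criteria, which reduces the number of later visits exposed.

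**A reader might see a contradiction with stopping for intolerable effects.** There is none: treatment can be stopped without knowing the arm.

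**An article may leave emergency procedures to the full protocol.** That would answer a silence. Here the article states an exclusive rule, and a full protocol that allowed safety unblinding would conflict with it.

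**Conclusion.** The rule is badly fixed as written. Three things follow from the text alone: the ground for unblinding is the endpoint itself, neither the size of change nor the level is defined, and a serious non-ocular adverse event is excluded as a ground.

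The bias argument is conditional. It needs the patient-level reading, actual use of the permission, and knowledge of the arm reaching the patient or an assessor. It is confined to groups 1–4 and 7–8. Under that reading, with the assumed 10-letter threshold and SD of change of 10, eligibility at one visit is 52% against 32% in favour of either arm, or 37.5% in both, depending on how the arms move. If the 120 patients were split equally over eight arms (15 each, an assumption because the figure is not shown), 52.3% and 31.7% are about 7.8 and 4.8 patients per arm. Neither the direction nor the size of any bias can be predicted from the documents. Even where the shares are equal, the patients concerned are still selected by outcome.

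Confidence is medium, chiefly because the level of unblinding is ambiguous.

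**What to change.** Rewrite the unblinding sentence in the Blinding section as follows.

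1. Remove change in primary outcomes, as such, as a ground for unblinding an individual.
2. Allow an individual code break when knowledge of the allocation is needed for that patient's safety. This can include ocular deterioration as well as non-ocular events.
3. Record the date and reason of each break, and keep outcome evaluators blind to the result.
4. State that a code break is not in itself a reason to exclude the patient from the analysis. Reconcile this with the Elimination Criteria, which remove patients who worsen and need conventional treatment, so that the two sections do not pull against each other.
5. If the sentence was meant for group-level unblinding at an interim analysis, move it there, say so, and define the criterion.

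The cost is about a paragraph of wording, plus the reconciliation with the Elimination Criteria, which needs a decision by the investigators. No extra patients, visits or measurements are required.

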### Outcome Measures

After enrollment, four study visits take place every 2 weeks during a follow-up period of 8 weeks in groups 1 and 2 (DME: placebo and levosulpiride) and groups 3 and 4 (NPDR: placebo and levosulpiride). For groups 7 and 8 (DME plus ranibizumab: placebo and levosulpiride) enrollment is followed by three visits, one every 4 weeks (at the time of ranibizumab intravitreal delivery). At each visit, the medical history, physical examination, adverse events, and primary and secondary outcomes are documented. For groups 5 and 6 (PDR requiring vitrectomy: placebo and levosulpiride), there is only one visit 1 week after enrollment, i.e., at the time of vitrectomy.

#### Objectives

The objectives of the study are to evaluate the effect of prolonged exposure to PRL induced by levosulpiride on DME and DR progression, evaluate the effect of levosulpiride as a combination therapy with ranibizumab on DME progression, and whether the actions of levosulpiride occur *via* the intraocular incorporation of PRL and its conversion to vasoinhibins. Therefore, the primary endpoints of the study medication are changes from baseline of ophthalmologic parameters and of PRL and vasoinhibin levels in the vitreous.

#### Primary Outcome Measures

Best-corrected visual acuity. Number of letters recognized in the ETDRS chart test after correcting for any refractive error (myopia, hyperopia, or astigmatism)Retinal thickness evaluated by OCT imaging *via* qualitative and quantitative analyses. For qualitative analyses, OCT images approaching the histological level of retinal morphology are interpreted based on normal and diseased features (hyper-reflective or hypo-reflective lesions, shadowing, and anatomical changes). Quantitative analysis evaluates retinal reflective signals and their correlation with retinal morphology by computer image-processing algorithms (retinal thickness map, volume, area, 1-, 3-, and 6-mm ETDRS circle diameters)Number, size, and location of retinal hard exudates and hemorrhages evaluated by fundus biomicroscopyLocation, area, and source of retinal microaneurisms, leakage area, cotton-wool spots, venous beading, micro-vascular, and vascular abnormalities evaluated by fundus fluorescein angiography imagingSerum and vitreous levels of PRL (IMMULITE 2000XPI immunoassay system)Vasoinhibin vitreous levels (immunoprecipitation-Western blot-densitometry)

#### Secondary Outcome Measures

The secondary endpoints evaluate the safety of the study medication by measuring:
Blood pressureBlood glycated hemoglobinSerum glucoseSerum creatinineHyperprolactinemia-related side effects documented at each participant visit (32)Dopamine D2 receptor blocker side effects documented at each participant visit (32)

### Sample Size

The proposed sample size (Figure 1) was calculated according to expected differences in visual acuity, the main parameter of visual function. Using the formula for mean differences and the reported changes in visual acuity (33, 34), we considered a difference of 10 letters in the ETDRS chart test between baseline and after intervention, a SD of 10, a power 1 − β = 80%, and a type-I error rate of 5%. For PRL and vasoinhibin level outcome, sample size is in accord to experimental models of DR and clinical experience (14, 15). As the study progresses, the study may need to accommodate a different sample size to obtain clinically relevant and statistically significant differences, access to eligible patients, elimination of patients, etc.

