## Methods/Design

### Study Setting and Sample

A total of 120 patients will be enrolled in this study over the course of 3 years. Recruitment takes place at an out-patient clinical Institution [Mexican Institute of Ophthalmology, Private Assistance Institution (Instituto Mexicano de Oftalmología, I.A.P.), Queretaro, Mexico] at the time of a routine health care or with patients referred from other out-patient clinics and health facilities. The principal investigators or investigators inform the patients (orally and in writing) about benefits and risks of participating in the study and of the clinical assessments and randomized allocation of treatment. Patients have to provide written consent before being enrolled and prior the initiation of any study-related assessment. Patients may withdraw their consent to participate at any time without providing a reason. There is no financial compensation for the study participation. However, all clinical evaluations and study medication have no cost for the patients.

Based on the current status, we expect a screening rate of 600 patients in 3 years, out of which about 120 are expected to meet the inclusion criteria, be willing to participate and, therefore, enrolled in the study. The dropout rate is expected to be less than 20%. The study may expand to a multicenter format if not enough patients are recruited.

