### Study Design

The study design is shown in Figure 1. This is a single-center, prospective, randomized, placebo-controlled, double-blind clinical trial on the efficacy and safety of levosulpiride for the treatment of DR and DME. An eight-armed study design is followed in which diabetic male and female subjects are selected from four different populations, those having DME, NPDR, PDR undergoing vitrectomy, and DME that will receive antiangiogenic therapy with ranibizumab. Ranibizumab is a humanized monoclonal antibody fragment directed against all forms of vascular endothelial growth factor (VEGF) approved as antiangiogenic therapy for DME (27). Immediately after baseline, each of the four groups is randomly split up into a subgroup that receives levosulpiride and a subgroup that receives placebo (lactose pill). Allocation is randomly assigned *via* computer-generated random numbers. The comparison of ophthalmologic and health outcomes between groups 1 and 2 (DME: placebo and levosulpiride) and groups 3 and 4 (NPDR: placebo and levosulpiride) will evaluate the efficacy and safety of the medication against DME and NPDR, respectively. Comparison between groups 7 and 8 (DME plus ranibizumab: placebo and levosulpiride) will investigate the benefits of levosulpiride treatment on top of standard antiangiogenic therapy with ranibizumab in advanced DME. Although anti-VEGF agents are the firstline therapy for DME involving the central macula, approximately 50% of the patients do not respond suggesting the contribution of other vasoactive and proinflammatory mediators (28). Vasoinhibins block the vascular effects of VEGF and of other cytokines present in the vitreous of DR patients (17, 18, 20, 29), implying that levosulpiride may extend and potentiate the benefits of the anti-VEGF therapy. The comparison of serum and vitreous PRL levels between the groups 5 and 6 undergoing vitrectomy (DR: levosulpiride and placebo) will serve as a proof of principle that PRL enters the eye to counteract disease progression. Blood samples are drawn immediately prior to surgery and before the induction of anesthesia.

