### Current Status

Patients started enrolling in this trial on May 2016. As of January 2018, 270 patients were screened and 63 identified as candidates signed the informed consent. Later nine patients were excluded (1 due to hyperprolactinemia, 6 because of glomerular filtration rates <30 mL/min, 1 due to glaucoma, and 1 requiring laser therapy). From the remaining 54 study subjects, 9 dropped-out after randomization (3 did not comply with the study medication, 2 missed outcome data, 1 required conventional therapy, and 3 vitrectomies were rescheduled as patients forgot to take hypertension medication before surgery and had very high blood pressure values), and 45 completed the study. Relevant protocol modifications will be registered at ClinicalTrials.gov. The protocol last amendment was registered on October 3, 2017 and consisted in the inclusion of DME patients receiving placebo or levosulpiride on top of standard antiangiogenic therapy with ranibizumab.

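### The 80% power is stated for a 10-letter change from baseline, but the efficacy comparison is levosulpiride against placebo; as a between-arm difference, equal arms of 15 would give about 75–78% before loss and 65–69% at 20% loss

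*Protocol article*

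**What the plan says.** The Sample Size section bases the trial on visual acuity: "Using the formula for mean differences and the reported changes in visual acuity", "we considered a difference of 10 letters in the ETDRS chart test between baseline and after intervention, a SD of 10", with "a power 1 − β = 80%, and a type-I error rate of 5" per cent. It does not say whether the formula is paired or two-sample, whether the SD of 10 belongs to a change or to a single measurement, or whether the test is one- or two-sided. It states no allowance for dropout. It refers to Figure 1 for the numbers, and it sizes the prolactin and vasoinhibin outcome on other grounds.

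The Study Design section sets the inference: "The comparison of ophthalmologic and health outcomes between groups 1 and 2", and likewise groups 3 and 4, is to establish efficacy, and groups 7 against 8 the benefit on top of ranibizumab. On size, "An eight-armed study design is followed" and "A total of 120 patients will be enrolled in this study over the course of 3 years". On loss, "The dropout rate is expected to be less than 20" per cent. Current Status reports that 9 of 54 patients dropped out after randomisation.

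**The concern.** A change from baseline in one arm mixes any drug effect with everything else that moves acuity over the follow-up: practice on the chart, regression to the mean and concomitant care. The placebo arm exists to remove these. Power for a within-patient change therefore says nothing about power for the difference between arms.

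The gap is plainest in groups 7 and 8. Enrollment and Randomization gives ranibizumab to both arms, so both could gain 10 letters with no levosulpiride effect at all. The relevant quantity there is the added effect, and the article gives no planning value for it.

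Two things are at stake. A non-significant comparison could be over-read as evidence of no effect because 80% power was stated. And a gain within the levosulpiride arm could be presented as the effect the trial was sized to find.

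**Working it through.** **Inputs.** Difference 10 letters, SD 10, power 80%, type-I error 5% (Sample Size); 120 patients, dropout below 20% (Study Setting and Sample); eight arms (Study Design); 9/54 = 16.7% lost so far (Current Status). Assumed: two-sided test, SD 10 is the SD of change and, where stated, equal arms of 120/8 = 15.

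**1. Can the plan's figure be reproduced?** The text gives no number per arm, so I tried both readings.

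- Change within one arm: n = (SD/difference)² × (1.960 + 0.842)² = 7.85, so 8 (normal formula), or 10 by the t-test.
- Difference between two arms: n = 2 × (SD/difference)² × (1.960 + 0.842)² = 15.7, so 16 per arm (normal), or 17 by the t-test.

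Neither fixes the total. Eight arms of 16 make 128. Six visual-acuity arms of 16 make 96, and 24 for groups 5 and 6 would bring that to 120. Without the arm sizes, the stated figure can be neither confirmed nor refuted.

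**2. Between-arm power** for 10 letters, SD 10, two-sided 5%. The normal formula is Φ(√(n/2) × 10/10 − 1.960); the t column uses the noncentral t distribution with 2n − 2 degrees of freedom.

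| Evaluable per arm | Normal | t-test |
|---|---|---|
| 12 (15 less 20%) | 68.8% | 64.9% |
| 13 | 72.2% | 68.7% |
| 15 (no loss) | 78.2% | 75.3% |
| 16 | 80.7% | 78.1% |
| 17 | 83.0% | 80.7% |

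With 12 per arm, the difference detectable at 80% power is about 12.0 letters (t-test).

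**3. Does another split of 120 reach 80% in all three visual-acuity populations?** Enrol 16/(1 − loss) (normal) or 17/(1 − loss) (t-test) per arm, rounded up, in six arms. Groups 5 and 6 take what remains.

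| Loss | Per arm, normal / t | Six arms | Left for groups 5 and 6 |
|---|---|---|---|
| 0% | 16 / 17 | 96 / 102 | 24 / 18 |
| 10% | 18 / 19 | 108 / 114 | 12 / 6 |
| 15% | 19 / 20 | 114 / 120 | 6 / 0 |
| 16.7% | 20 / 21 | 120 / 126 | 0 / none (6 short) |
| 20% | 20 / 22 | 120 / 132 | 0 / none (12 short) |

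The largest arm that leaves anyone for groups 5 and 6 is 19. It tolerates a loss of 1 − 16/19 = 15.8% (normal) or 1 − 17/19 = 10.5% (t-test).

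**4. Sensitivity to what is not stated.**

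- One-sided 5%: 13 (normal) or 14 (t) evaluable per arm suffice. At 20% loss that is 17 or 18 enrolled, 102 or 108 in six arms, which fits within 120. Power at 12 per arm is 79% or 77%.
- SD 10 as the SD of a single measurement: the SD of change is 10√(2(1 − ρ)). At 12 per arm, normal-formula power is 54% for ρ = 0.3, 69% for 0.5 and 89% for 0.7 (ρ assumed).
- Purely as an illustration, if levosulpiride added 5 letters to ranibizumab, t-test power would be about 22% at 12 per arm and 26% at 15.

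**The case against.** The strongest reply is that this is loose wording and not a wrong calculation. The abstract defines the endpoints as changes from baseline, the Study Design section is explicit that arms are compared, and the paired formula gives only 8 to 10 per group, whereas the two-sample formula gives 16, close to 15. That is plausible, and a reader should not infer that a paired formula was used; the text does not show it. But as printed, the 80% is attached to a change from baseline, and nothing in the article gives the between-arm difference.

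It is also tempting to infer that no division of 120 patients can deliver 80%, or that all three visual-acuity comparisons fall short. The documents do not support either. Groups 5 and 6 are sized separately and need not match the other arms; with no loss, 6 × 16 + 24 or 6 × 17 + 18 works. The real arm sizes are in Figure 1. The 20% is an upper bound, and three of the nine losses so far were rescheduled vitrectomies, so the rate in the visual-acuity arms alone is not given.

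Nor should recruitment to January 2018 be projected into a final power. Groups 7 and 8 came in with an amendment registered in October 2017, so the earlier rate does not describe the eight-arm trial, and expansion to more centres is foreseen.

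Finally, the article allows that the sample size may change, and a fuller document may hold a dropout allowance. That tempers the criticism about loss, but it does not correct the planning quantity.

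**Conclusion.** The Sample Size statement is wrong as written: it claims 80% power for a quantity that the trial's efficacy comparisons do not test. That conclusion needs no assumption about arm sizes.

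The size of any shortfall is conditional. It rests on a two-sided 5% test, 10 letters as the between-arm difference, 10 as the SD of change, and equal arms of 15. The shortfall is then modest before loss, 2 to 5 points below 80%, and 11 to 15 points at the dropout bound. With the arms freely sized, 80% in all three populations is compatible with keeping patients for groups 5 and 6 up to about 15% loss (normal) or 10% (t-test). It is not compatible at the 16.7% overall loss reported so far, or at 20%. A one-sided test or another meaning of the SD would change these figures, which is itself a reason to state both.

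**What to change.** In the Sample Size section:

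- Restate the planning difference as the difference between levosulpiride and placebo in change in best-corrected visual acuity from baseline. For groups 7 and 8, make it the effect added to ranibizumab.
- State what the SD of 10 refers to, whether the test is one- or two-sided, the number per arm and the dropout allowance.
- Give the power, or the difference detectable at 80%, that remains after expected loss. With equal arms of 15 and the assumptions above, that is 65–69%, or about 12 letters by the t-test, at 20% loss.
- Say that change within an arm is descriptive only.
- Compare arms by ANCOVA with baseline acuity as covariate; the Enrollment and Randomization section already collects it. If the SD of change is 10 and the baseline–follow-up correlation is ρ (assumed 0.5 to 0.8), the residual SD is 10√((1 + ρ)/2), or 8.7 to 9.5. With 2n − 3 degrees of freedom, power is then about 77% to 69% at 12 per arm and 86% to 79% at 15.

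This requires no extra patients, visits or measurements. The downside is a less favourable stated power, only partly recovered by the baseline adjustment.
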